### Measures

Patients will complete self-report, pen and paper measures. Clinical vaginal assessments will be completed by the treating clinician. Table 
1 presents when measures will be administered.

**Table 1 T1:** Time-points for collection of patient reported outcomes and clinical outcomes for the PeNTAGOn study

**Time-point**	**Questionnaire**
Baseline & clinical exam I: (pre-treatment)	Demographic and clinical variables, HADS, FACT-G, SCNS-SF34-R, MSAS-SF, SVQ, clinical exam I (LENT SOMA scale)
Follow-up 1: (immediately prior to first radiotherapy)	HADS, CaTS
Follow-up 2: (4 weeks post radiotherapy and post intervention)	HADS, FACT-G, SCNS-SF34-R, MSAS-SF, AQ, CaTS and Patient Care evaluation & Referrals
Clinical exam II (3 months post radiotherapy)	Clinical exam II (LENT SOMA scale)
Follow-up 3 & clinical exam III: (6 months post radiotherapy)	HADS, FACT-G, AQ, SVQ, clinical exam III (LENT SOMA scale)
Follow-up 4 & clinical exam IV: (12 months post radiotherapy)	HADS, FACT-G, AQ, SVQ, clinical exam IV (LENT SOMA scale)

AQ, Adherence questionnaire; CaTS, Cancer Treatment Survey; FACT-G, Functional Assessment for Cancer Therapy - General; HADS, Hospital Anxiety and Depression Scale; LENT SOMA, Late Effects of Normal Tissues / Subjective-Objective Management Analytic; MSAS-SF, Memorial Symptom Assessment Scale Short Form; SCNS-SF34-R, Supportive Care Needs Survey - short form, Revised response format; SVQ, Sexual function-vaginal changes questionnaire.

#### Demographics and clinical variables

Demographic details will be recorded by the patient on the baseline questionnaire and include age, postcode, marital and education status, employment situation and occupation, living arrangements, whether they have children, sexual orientation, country of birth and first language, menopausal status, and antidepressant or sedative use. Clinical details of diagnosis, diagnosis date, disease stage, Eastern Cooperative Oncology Group (ECOG) performance status, histopathology grade, history of another cancer, treatment for a past diagnosis, current treatment type (external beam, brachytherapy, concurrent chemotherapy), prior treatments (surgery, chemotherapy), involvement with hospital services and Charlson co-morbidity index will be completed by the data manager on a case record form.

#### Clinical examination

The treating clinician will conduct clinical vaginal examinations. The LENT SOMA scale (Late Effects of Normal Tissues / Subjective-Objective Management Analytic), objective criteria for vaginal/sexual dysfunction
[50,51] will be used to measure vaginal changes.

#### Psychological distress

Psychological distress will be assessed with the 14-item HADS total scale (HADS-T)
[52]. Rasch analysis shows that items comprising the HADS-T form a unidimensional construct of psychological distress
[53]. It has demonstrated high internal consistency (alpha=0.82 to 0.90) in patient populations including cancer patients
[54,55] and responsiveness in psychosocial intervention studies
[56,57].

#### Cancer-specific quality of life

Cancer-specific quality of life will be assessed with the 27-item Functional Assessment for Cancer Therapy - General (FACT-G). The FACT-G comprises four subscales for specific quality of life domains: physical, social, emotional and functional wellbeing. Scaling and unidimensionality of subscales have been confirmed by factor and Rasch analyses
[58,59]. All subscales have demonstrated high internal consistency (alpha=0.72 to 0.90), good convergent (r>0.51), divergent (r<0.22) and discriminative validity in cancer patients
[45] and responsiveness in psychosocial intervention studies
[57,60].

#### Unmet supportive care needs

The 34-item Supportive Care Needs Survey-short form with revised response format (SCNS-SF34-R)
[61,62] covers unmet needs from five domains: psychological; health system and information; physical and daily living; patient care and support; and sexuality. All domain subscales have high internal consistency (alpha≥0.87) and good divergent and convergent validity
[63]. Aranda, Schofield and colleagues found this scale to be responsive to change in a recent RCT with cancer patients
[64].

#### Symptom distress

The 32-item Memorial Symptom Assessment Scale Short Form (MSAS-SF)
[65] comprises three subscales (physical, psychological and global distress) and a total symptom distress scale. All scales have demonstrated high internal consistency (alpha=0.76 to 0.87), good convergent validity (r =−0.68 to −0.74), excellent discriminative validity based on known groups comparisons
[65] and sensitivity to change in a longitudinal setting
[66].

#### Sexual function and vaginal changes

The 27-item Sexual function-vaginal changes Questionnaire (SVQ)
[67], developed for gynaecological cancer, comprises three scales for all patients (intimacy, sexual interest and global sexual satisfaction) and two scales for sexually active respondents (vaginal changes and sexual functioning). All five scales have demonstrated high internal consistency (alpha =0.76 to 0.83)
[68] and sensitivity to change longitudinally
[67].

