#### Secondary endpoints

Compared to the usual care group, the intervention group will report:

1. Lower informational and psychosocial supportive care needs and lower symptom distress from baseline to follow-up at 4 weeks post treatment,

2. Better preparation for treatment from first follow-up immediately prior to the first radiotherapy treatment to follow-up at 4 weeks post treatment,

3. Higher psychosexual functioning from baseline to follow-up at 6 and 12 months post treatment,

4. Higher quality of life from baseline to follow-up at 4 weeks post treatment, and

5. Less vaginal stenosis at 3, 6 and 12 months post treatment.

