##### Intervention session 3: end of treatment, face-to-face, 30 minutes

Some patients report relief upon completing treatment however research by Jefford *et al*. has shown that this is often a time of uncertainty and anxiety
[43]. This may be compounded by treatment side effects, both acute and long-term
[2,5,6,14]. In this session the woman can discuss anxieties related to treatment completion, ongoing issues and treatment side effects with the nurse. Vaginal health and psychosexual recovery will be explored, including the resumption of sexual activity if desired. The nurse will provide the patient with a Survivorship Care Plan (SCP) detailing the woman’s diagnosis and treatment received, planned follow-up schedule, common ongoing or new treatment side effects, and how to manage them. With the patient’s permission, the nurse will fax a copy of the SCP to the patient’s primary care doctor.

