#### Outcome analysis

Outcome analyses will be carried out by fitting linear mixed models (LMM) to each outcome separately. In this case, a sequence of two-level models including random intercepts and slopes will be constructed for each outcome following recommended procedures
[70]. Fully parameterised models will also include fixed effects for time (linear and higher-order polynomials, as appropriate), group, site plus all two-way and cross-level interactions. LMM use all available data, which supports an intention-to-treat approach, and adjusts variance estimates for the correlation between repeated measurements on the same participants. Potential confounders (that is, patient characteristics such as age) will be included as co-variates. These will be centred to facilitate accurate interpretation of results and will be retained in the final models if they explain significant variation in outcomes and improve the precision of the estimates of the treatment effect.

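### Two of the five SVQ scales are defined only for sexually active women, so an arm comparison on them at 6 and 12 months is not protected by randomisation, is not intention-to-treat and may be biased

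*Protocol article*

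**What the plan says.** The section on sexual function and vaginal changes says that the SVQ "comprises three scales for all patients (intimacy, sexual interest and global sexual satisfaction") and, in addition, "two scales for sexually active respondents (vaginal changes and sexual functioning"). Table 1 under Measures schedules the SVQ at baseline and at 6 and 12 months after radiotherapy; the 6-month row reads "HADS, FACT-G, AQ, SVQ, clinical exam III (LENT SOMA scale").

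Secondary endpoint 3 is "Higher psychosexual functioning from baseline to follow-up at 6 and 12 months post treatment". It names no SVQ scale, but the SVQ is the sexual-function questionnaire in the schedule and its visits match the hypothesis.

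On the intervention side, nurse session 3 states: "Vaginal health and psychosexual recovery will be explored, including the resumption of sexual activity if desired". Session 1 also covers psychosexual rehabilitation.

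The outcome analysis section says: "Outcome analyses will be carried out by fitting linear mixed models (LMM) to each outcome separately". It adds: "LMM use all available data, which supports an intention-to-treat approach". Nothing separates the two restricted SVQ scales from the outcomes to which this applies.

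**The concern.** For the vaginal changes and sexual functioning scales, the available data come only from women who are sexually active. At 6 and 12 months, that status arises after randomisation and after an intervention that discusses it. Comparing arms among active women therefore compares two subgroups that the intervention may itself have shaped.

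A mixed model on all available data does not remove the difficulty. Its usual justification is that an unobserved score exists and is missing at random given what was observed. An inactive woman's score on these scales is not missing; it is undefined. The all-randomised contrast implied by intention-to-treat does not exist for these two scales.

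What is at stake is how hypothesis 3 is read. Suppose the intervention helps women with more difficulties to resume activity. The active group in that arm would then contain more women with poor scores, and the scale could show no benefit, or apparent harm, because the intervention had worked on activity.

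**Working it through.** **1. The benchmark.** The sample size section assumes 0.35 SD for continuous outcomes, a 5% level (two-sided assumed), at least 80% power and 130 per arm at 12 months.

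- n per arm = 2(1.960 + 0.842)² / 0.35² = 128.2, so 129; the t-test version gives 129.1, so 130. Power at 130 per arm is 80.6%.
- Number randomised: 260 / 0.85 = 305.9, so 306; also 600 × 0.85 × 0.60 = 306.

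The plan's figures reproduce. The 0.35 SD serves below only as a yardstick.

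**2. Selection illustration.** The documents give no activity rates and no relation between activity and score, so every input here is an assumption.

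- Latent score Y ~ N(0,1), higher meaning better function, with no treatment effect.
- A woman is active if a standard normal variable with correlation ρ to Y exceeds a cut-off that gives the arm's active proportion p.
- Mean score among active women: E[Y | active] = ρ·φ(z_p)/p, where z_p is the cut-off and φ the normal density.

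With 45% active under usual care, φ(z)/p = 0.880. With 60% active under the intervention, it is 0.644. The difference is −0.236 × ρ:

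| ρ | Spurious difference (SD) | Share of 0.35 SD |
|---|---|---|
| 0 | 0 | 0% |
| 0.3 | −0.07 | 20% |
| 0.5 | −0.12 | 34% |
| 0.7 | −0.17 (−0.165) | 47% |

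The size depends on the assumed rates. At ρ = 0.5:

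- 40% versus 45% active gives −0.04
- 40% versus 50% gives −0.08
- 30% versus 45% gives −0.14
- 40% in both arms gives 0

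**3. Does the mixed model remove it?** A random-intercept model with known variances was fitted to 2,000,000 simulated women with scores at baseline, 6 and 12 months, present only when a woman was active. The assumptions were 40% active at baseline in both arms, half of the score variance between women, and a true effect of zero. With 40% versus 55% active at follow-up:

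| ρ | Difference at each follow-up (SD) | As change from baseline (SD) |
|---|---|---|
| 0 | 0.00 | 0.00 |
| 0.3 | −0.07 | −0.06 |
| 0.5 | −0.12 | −0.10 |
| 0.7 | −0.17 | −0.14 |

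With 40% active in both arms and ρ = 0.5, the differences were zero within simulation error. Repeated measures and a baseline score therefore reduce the artefact only slightly.

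**The case against.** The strongest reply is that the article does not expressly say the arms will be compared on the two restricted scales. The SVQ section describes how the questionnaire is built, hypothesis 3 names no scale, and the analysis section speaks of outcomes in general. Which scales carry the hypothesis, and how inactive women are handled, are details that a condensed article may leave to a fuller plan. All of that stands. What remains is the text that is given: one model for every outcome on all available data, with an intention-to-treat rationale. Followed as written, that does not suit these two scales.

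A reader might go further and infer that the comparison is biased as a matter of fact. The documents do not support this. Bias needs both an effect of the intervention on who is active and a link between activity and score, and neither is quantified. Resumption of activity is raised only "if desired" by the woman, as the session 3 text puts it, and raising sexual activity is not among the stated aims. The illustration also gives inactive women a latent score that the real scale does not define. It shows direction and order of size and predicts nothing for this trial. In the illustrated direction the error runs against the intervention, so it would not create a false benefit.

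A reader might also infer that the randomised evidence on psychosexual outcomes is lost. It is not. Three SVQ scales cover all patients, and vaginal change is also assessed by clinician examination (LENT SOMA) at baseline, 3, 6 and 12 months, which the article does not restrict to sexually active women.

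**Conclusion.** The point holds in a limited form. Any arm comparison on the vaginal changes and sexual functioning scales at 6 and 12 months is made within a post-randomisation subgroup. It is not an intention-to-treat comparison, and fitting a mixed model to all available data does not make it one. This follows from the article's own description of the scales, the visit schedule and the intervention content.

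Whether bias would result is open. Under the assumed 45% versus 60% active and correlations of 0.3 to 0.7, it is −0.07 to −0.17 SD, or 20% to 47% of the 0.35 SD design effect. It is zero if the intervention does not change who is active, or if activity is unrelated to the score. Only part of one secondary endpoint is affected. The primary HADS-T comparison and the sample size are untouched.

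**What to change.** - Test hypothesis 3 on the three SVQ scales defined for all patients: intimacy, sexual interest and global sexual satisfaction.
- Report sexual activity (yes/no) by arm at 6 and 12 months as an outcome in its own right.
- Present the two restricted scales as supportive or descriptive, beside the activity proportions. If an inferential comparison is wanted, state the estimand and add a sensitivity analysis for selection into activity.
- Exclude the two restricted scales from the intention-to-treat statement in the outcome analysis section.

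These choices should be fixed before outcome data are examined, because the statistical analyses section allows methods to be revised after inspection of the data. Recruitment was open at publication.

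The cost is analysis wording. The instrument and visits stay the same, provided activity status is recorded at each SVQ visit, as the restricted scales imply. The downside is that the two restricted scales can then only support the conclusion on psychosexual functioning and cannot carry it.

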#### Cancer treatment-related information and support needs

Schofield *et al*. developed a 25-item Cancer Treatment Survey (CaTS)
[69] which comprises two subscales for specific information and support needs domains: sensory-psychological concerns and procedural concerns. Both subscales have demonstrated high internal consistency (alpha>0.90) and good divergent validity (with HADS: r<0.26)
[69]. Both were sensitive to change in a recent RCT
[29].

#### Adherence questionnaire and patient care evaluation

Adherence to use of vaginal dilator, moisturiser, lubricant and pelvic floor exercises will be assessed with a purpose designed Adherence questionnaire (AQ). Patients’ perceived global rating of change in psychological distress from baseline and experience of referrals from commencement of treatment will be assessed with a patient care evaluation questionnaire, also purpose designed.

### Statistical analyses

All data will be analyzed through SPSS Windows Version 20.0 (SPSS, Chicago, IL, USA). After inspection of the data, the appropriateness of all methods described below will be reviewed and revised if necessary.

#### Preliminary analysis

Descriptive statistics will be used to summarise baseline data, compliance with questionnaires and reasons for non-compliance by study arm. Parametric and non-parametric tests of association and mean differences as appropriate will be used to assess recruitment bias and possible differential attrition for consenting participants.

#### Outcome analysis

Outcome analyses will be carried out by fitting linear mixed models (LMM) to each outcome separately. In this case, a sequence of two-level models including random intercepts and slopes will be constructed for each outcome following recommended procedures
[70]. Fully parameterised models will also include fixed effects for time (linear and higher-order polynomials, as appropriate), group, site plus all two-way and cross-level interactions. LMM use all available data, which supports an intention-to-treat approach, and adjusts variance estimates for the correlation between repeated measurements on the same participants. Potential confounders (that is, patient characteristics such as age) will be included as co-variates. These will be centred to facilitate accurate interpretation of results and will be retained in the final models if they explain significant variation in outcomes and improve the precision of the estimates of the treatment effect.

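### Random slopes are prescribed for every outcome, but three secondary instruments are measured only twice; the variance components are then not identified and no replacement model is named, although the treatment contrast stays estimable

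*Protocol article*

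**What the plan says.** The Outcome analysis section plans linear mixed models for each outcome separately and states that "a sequence of two-level models including random intercepts and slopes will be constructed for each outcome", citing a published model-building procedure. The full models also contain "fixed effects for time (linear and higher-order polynomials, as appropriate), group, site plus all two-way and cross-level interactions". No exception is made for outcomes with few measurements.

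Table 1 (Measures) fixes the occasions:

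- Baseline: "Demographic and clinical variables, HADS, FACT-G, SCNS-SF34-R, MSAS-SF, SVQ, clinical exam I (LENT SOMA scale").
- Follow-up 1: the HADS and the CaTS only.
- Follow-up 2: "HADS, FACT-G, SCNS-SF34-R, MSAS-SF, AQ, CaTS and Patient Care evaluation & Referrals".
- 6 months: "HADS, FACT-G, AQ, SVQ, clinical exam III (LENT SOMA scale"). 12 months: "HADS, FACT-G, AQ, SVQ, clinical exam IV (LENT SOMA scale").

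The SCNS-SF34-R and MSAS-SF therefore appear twice (baseline, follow-up 2), and so does the CaTS (follow-ups 1 and 2). Under Secondary endpoints, hypothesis 1 is "Lower informational and psychosocial supportive care needs and lower symptom distress from baseline to follow-up at 4 weeks post treatment" and hypothesis 2 is "Better preparation for treatment from first follow-up immediately prior to the first radiotherapy treatment to follow-up at 4 weeks post treatment". Each spans exactly the two occasions available.

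The opening of Statistical analyses allows every method to be reconsidered and changed once the data have been inspected. It names no alternative.

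**The concern.** The article commits all outcomes to one model class, and its own measurement schedule cannot support that class for three instruments. This is more than detail left to an analysis plan, because the stated model and the stated schedule do not fit together. At stake is how two secondary hypotheses are analysed. An analyst who fits the model as written gets variance components with no unique value and perhaps a software warning, and must then pick something else. As written, that choice falls under the review after data inspection, in a trial where patients and providers are not blinded. The mismatch is visible from the schedule alone, so it can be settled before any outcome is seen.

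**Working it through.** **Plan's own figure.** The article gives no figure on this point. The only related number is the sample size, which is sound and is not in question: 0.35 SD, 80% power and 5% significance (two-sided assumed) give 129 per arm by the normal approximation and 129.1, rounded up to 130, by the t-test. The check below uses 130 per arm.

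**Occasions, counted from Table 1.** HADS 5, FACT-G 4, SVQ 3, SCNS-SF34-R 2, MSAS-SF 2, CaTS 2.

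**Identification.** Let g00 be the intercept variance, g11 the slope variance, g01 their covariance and s2 the residual variance. With two occasions scored t = 0 and t = 1 for everyone:

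- Var(y1) = g00 + s2
- Cov(y1, y2) = g00 + g01
- Var(y2) = g00 + 2·g01 + g11 + s2

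This is three equations in four unknowns, and the rank is 3 of 4. Raising s2 by d, lowering g00 by d, raising g01 by d and lowering g11 by 2d leaves all three moments unchanged. With three or five occasions the rank is 4 of 4.

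**Numerical check.** Simulated data, 260 patients, both variances 1, assumed correlation 0.5:

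| s2 | g00 | g01 | g11 | log-likelihood | group-by-time estimate | SE |
|---|---|---|---|---|---|---|
| 0.05 | 0.95 | -0.45 | 0.90 | -181.408 | -0.197 | 0.124 |
| 0.20 | 0.80 | -0.30 | 0.60 | -181.408 | -0.197 | 0.124 |
| 0.40 | 0.60 | -0.10 | 0.20 | -181.408 | -0.197 | 0.124 |

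All three random-effects matrices are valid and fit equally well, so the components are not identified. The treatment contrast does not move, because its variance depends only on the total covariance matrix:

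(2/n)·[Var(y1) + Var(y2) − 2·Cov] = (2/130)·(1 + 1 − 1) = 0.01538, so SE = 0.124.

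**Versions that escape the problem.** Each needs a choice that the article does not state.

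- Intercept and slope uncorrelated, time coded 0/1: rank 3 of 3, but Var(y2) − Var(y1) = g11, so the second variance must be at least the first. With time centred at −0.5 and 0.5, rank 2 of 3.
- Individually varying elapsed times: rank 4 of 4.

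**Precision of the replacement.** With equal variances and correlation r, the arm difference has variance proportional to 1 − r² when follow-up 2 is adjusted for baseline, and to 2(1 − r) for change. The ratio is (1 + r)/2. The documents give no r, so these values are assumptions:

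| r | adjusted | change | ratio |
|---|---|---|---|
| 0.4 | 0.84 | 1.20 | 0.70 |
| 0.5 | 0.75 | 1.00 | 0.75 |
| 0.6 | 0.64 | 0.80 | 0.80 |

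Simulation gave ratios of about 0.70 to 0.81 over the same range.

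**CaTS.** Its first measurement comes after allocation and after the pre-treatment nurse session, so it is an outcome and not a baseline. If the intervention improved preparation equally at both occasions, the change contrast would be zero.

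**The case against.** The strongest reply is that no between-arm test is lost. A reader might infer that hypotheses 1 and 2 cannot be tested, that the models will not converge, or that their standard errors will be unreliable. The calculations do not support this. In further simulations of 260 patients, with the second variance 0.7, 1.0 or 1.4 times the first, the random-intercept, random-slope and change-score analyses agreed to four decimals on complete data. With 15% missing at the second occasion, the two mixed models differed by at most 0.006 in estimate and 0.003 in standard error. All six random-slope fits reported convergence, though in statsmodels and not in SPSS, which the article names. This part of the reply stands in full.

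Second, building models in sequence leaves room to drop an unsupported slope, and the covariance structure and time scoring may be set out in a fuller document. That is fair, and it makes non-identification conditional. But the article says random slopes for each outcome and does not say that they may be dropped.

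Third, a reader might add that polynomial time terms cannot be fitted to two points. The article includes them only as appropriate, so this is already covered and is not part of the point.

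Fourth, regressing follow-up 2 on baseline drops patients without follow-up 2, whereas the article favours using all available data. This is a reasonable objection to plain regression, and the fix offers a model that avoids it.

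**Conclusion.** The point holds in a limited form. With common nominal times and a free intercept-slope covariance, the model prescribed for the SCNS-SF34-R, MSAS-SF and CaTS has four variance parameters and three moments to estimate them from. This touches two of five secondary hypotheses and leaves the primary outcome, FACT-G and SVQ alone. The treatment contrast remains estimable. What is lost is the meaning of the variance components, possibly a clean model fit, and a replacement fixed before the data are inspected. Because the random-slope and random-intercept models give nearly the same treatment result, the scope for a favourable post-data choice between those two is small. The choice between a change contrast and a baseline-adjusted one matters more: a variance ratio of 0.70 to 0.80 for assumed correlations of 0.4 to 0.6, with equal variances. It is worth correcting because it costs so little.

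**What to change.** Add to Outcome analysis that outcomes measured on two occasions are analysed without a random slope, and name the model:

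- **SCNS-SF34-R and MSAS-SF:** estimate the arm difference at follow-up 2 adjusted for baseline score, treating hospital and treatment type (the two stratification factors in Study integrity). Use linear regression or, to keep all available data, a two-occasion model with unstructured covariance and a common baseline mean for both arms. The common mean is reasonable because patients learn their allocation only after returning the baseline questionnaire.
- **CaTS:** use categorical time with an unstructured 2×2 covariance, and report the arm difference at follow-up 1 and at follow-up 2. State that hypothesis 2 is read as better preparation at these two points. The change contrast can still be taken from the same model if wanted.
- **Outcomes with three or more occasions:** no change is needed on this account.

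The cost is a few sentences of analysis text, fixed before the data are inspected. Data collection, visits and sample size do not change.

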## Methods

### Design and setting

The trial takes place in six sites from three states of Australia. All sites are public hospitals, with two sites part of a specialist oncology facility. The volume of patients through each centre differs, so sites will not contribute equally to participant recruitment.

Ethical approval has been obtained from the Human Research Ethics Committees of participating states (Peter MacCallum Cancer Centre Ethics Committee, Project No: 09/07; Ethics Review Committee Royal Prince Alfred Zone, Project No: X11-0112 & HREC/11/RPAH/154; Royal Brisbane & Women’s Hospital Human Research Ethics Committee, Ref No: HREC/11/QRBW/202).

This study is a multicentre, prospective, randomised controlled intervention trial for patients receiving radiotherapy for gynaecological cancer, with follow-up of 1 year post-end of treatment.

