### Sample size

The treatment effect is conservatively estimated to result in group differences of 0.35 standard deviations for continuous outcome measures
[45-47]. With the Hospital Anxiety and Depression Scale total score (HADS-T) as the primary outcome, to achieve ≥80% power at a 5% significance level, the required sample size in each arm is 130 at the 12-month follow-up. With a patient approach rate estimated at 85%, consent rate estimated at 60% and attrition estimated at 15%, 600 participants will need to be approached to achieve a sample of 260.

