### Study integrity

The study design and reporting will adhere to the Consolidated Standards of Reporting Trials (CONSORT) statement
[48]. Usual care practice will be monitored yearly with a questionnaire administered to nurses most involved with the usual care of women with GC receiving radiotherapy at each site. A consecutive sample will be randomly allocated at the central site by computer with a weighted-biased coin method 1:1 to either intervention or usual care arms. Participants will be stratified according to treating hospital and treatment type. Minimisation will be used to balance the randomisation across the strata.

Participants will not be informed of their allocation until the baseline questionnaire has been received. Blinding of patients and providers to experimental arm cannot be achieved with this study design, however outcome assessment will be by self-reported questionnaire, thereby obviating the need for researcher blinding. Usual care arm participants will receive a booklet on their specific cancer diagnosis, treatment, and psychosexual recovery to meet minimal ethical standards
[49], and information will be provided as per usual practice by their treatment team. Reasons for attrition will be recorded and recruitment and dropout bias assessed.

All nurse and peer sessions will be audio-taped and a random sample of 15% of sessions will be assessed for adherence to protocol. Length of sessions will be reported. The first five calls or consultations made by each peer and nurse will be reviewed and feedback provided on adherence to protocol, use of communication and coaching skills and areas for improvement.

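### The full outcome model crosses group with site at six unequal sites and gives no rule for dropping or averaging these terms, so the group effect at a visit, and on one reading the group-by-time effect, depends on unstated choices

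*Protocol article*

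**What the plan says.** Under Outcome analysis, each outcome gets a linear mixed model: "a sequence of two-level models including random intercepts and slopes will be constructed for each outcome following recommended procedures". The fully parameterised version has fixed effects for time (linear and higher-order), "group, site plus all two-way and cross-level interactions". Potential confounders are added as covariates and "will be retained in the final models if they explain significant variation in outcomes" and sharpen the treatment estimate. That rule is written for covariates and does not mention the site interactions.

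On the sites, Design and setting says "The trial takes place in six sites from three states of Australia" and "The volume of patients through each centre differs, so sites will not contribute equally to participant recruitment". No site shares are given.

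On allocation, Study integrity says "Participants will be stratified according to treating hospital and treatment type", with minimisation across those strata. Site is in the model. Treatment type is not named there.

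The Sample size section plans for "group differences of 0.35 standard deviations for continuous outcome measures", with 130 per arm, at least 80% power and 5% significance. The primary hypothesis concerns distress from baseline to the first follow-up and to 4 weeks after treatment, which is a group-by-time effect.

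**The concern.** The trial asks one question about one package across six hospitals, and its size is that of a plain two-group comparison. Once group is crossed with site, the model holds six site-specific group effects at each visit. A single result then needs a weighting, and the article gives none. If a small site counts as much as a large one, the average is less precise than the sample size assumed.

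The phrase about cross-level interactions adds a second uncertainty. In a two-level model of visits within patients, time is at level 1, and group and site are at level 2. Group by time and site by time are thus cross-level terms, and they are already among the two-way terms. The phrase may simply overlap with what precedes it, or it may add group by site by time. Only in the second case does the group-by-time effect also become site-specific.

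A smaller point concerns treatment type. As written, it could enter only through the significance-based covariate rule, so whether the analysis respects a factor used in the allocation would depend on the data.

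**Working it through.** **Inputs from the protocol article.** 130 per arm (260 in all), effect 0.35 SD, 5% significance, at least 80% power, 15% attrition, six sites, 1:1 allocation.

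**Assumptions.** A two-sided test, arms balanced within site, the same true effect at every site, and the site shares shown below.

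**1. The plan's own figure.** A two-sided two-sample t-test with 130 per arm and 0.35 SD has 80.3% power (80.0% with 129). The recruitment chain also agrees: 600 × 0.85 × 0.60 = 306, and 306 × 0.85 = 260. The stated size reproduces as a plain two-group comparison without site interactions.

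**2. Group effect at one visit, group by site fitted, sites weighted equally.** With share p_j at site j, the site's group difference has variance 4/(260 p_j) in SD units. The equal-weight average of six has variance (1/36) × Σ 4/(260 p_j), against 4/260 without the interaction. The inflation is (1/36) × Σ(1/p_j). Power comes from the noncentral t with effect 0.35/√inflation.

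| Assumed shares (%) | Σ(1/p_j) | Inflation | Power |
|---|---|---|---|
| six equal sites | 36.0 | 1.00 | 80% |
| 25/20/20/15/10/10 | 40.7 | 1.13 | 75% |
| 35/25/15/10/10/5 | 53.5 | 1.49 | 64% |
| 50/20/10/10/5/5 | 67.0 | 1.86 | 54% |

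Weighting each site by its share instead gives variance Σ p_j² × 4/(260 p_j) = 4/260. Power from the same model is then 80.3% for every split.

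**3. Group-by-time effect in a mixed model.** Further assumptions: shares 40/25/15/10/5/5%, 260 patients, three equally spaced visits, linear time, random-intercept variance 0.6, residual variance 0.4, no random-slope variance, and sites weighted equally.

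| Model | SE of group by time |
|---|---|
| no group by site | 0.0555 |
| group by site added | 0.0555 |
| group by site by time also added | 0.0735 |

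The two-way model leaves the SE unchanged. The three-way term multiplies the variance by (0.0735/0.0555)² = 1.75, which matches step 2 for these shares: (1/36) × 63.17 = 1.75. With a random-slope variance of 0.02 the pattern is the same (0.0582, 0.0582, 0.0771).

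**4. Step 2 against the mixed model.** For the same shares and assumptions, the SE of the group effect at the first visit is 0.1198 without group by site, 0.1512 with it and 0.1587 with the three-way term. The variance ratios are (0.1512/0.1198)² = 1.59 and (0.1587/0.1198)² = 1.75. On the two-way reading, the single-visit figures in step 2 therefore somewhat overstate the loss in the repeated-measures model.

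**The case against.** The strongest reply is that the fully parameterised model is the top of a sequence and need not be the final one. The sequence follows a cited procedure that is not shown, and the article speaks separately of final models. The simplest reading of the interaction phrase names no three-way term, and on that reading the effect behind the primary hypothesis is common to all sites and keeps its precision. Equal weighting is not stated anywhere, and naming the contrast is ordinary analysis-plan detail.

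Much of this stands. A reader might infer that the model yields no single treatment effect, or that the trial will lose much of its 80% power. The article does not support either. The first is true only of the group effect at a visit, or if a three-way term is fitted. The second needs both unequal weighting relative to site size and site shares that are not given. A reader might also suppose that the result will be read from one reference hospital's coefficient. That would be very imprecise, but nothing in the article suggests it.

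The reply does not remove the point. The interaction structure is stated, and the only retention rule shown is for covariates. The Statistical analyses section also allows methods to be revised after the data are inspected, so the choice between models could follow the results. Treatment type could still enter as a covariate, so that part is an unfixed choice and not an exclusion.

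**Conclusion.** The point holds in a limited form. The stated full model contains group by site and may contain group by site by time, and the article does not fix when they go or how site effects are averaged.

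- For the group effect at a visit, equal site weighting costs about 5 percentage points of power under mild assumed imbalance and about 16 to 26 points under moderate to strong imbalance (80% to 64% or 54%). The cost is zero with equal sites or size weighting.
- For group by time, the cost is zero on the two-way reading. If the three-way term is fitted and sites are weighted equally, the loss is of the same order as for the group effect.

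These sizes rest on assumed site shares, a common effect across sites and a software default that the article does not state. They show what is left open and do not predict the trial's actual power. The change is worth making because it costs little and takes the primary comparison out of reach of a data-led choice.

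**What to change.** State one primary inferential model in the Outcome analysis section. Site and treatment type are always kept as main effects, whatever their significance, and there is one group-by-visit effect common to all sites. Group by site and group by site by time move to a separate analysis of heterogeneity between sites, labelled exploratory.

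The cost is a sentence or two of analysis wording, with no new data and no change to sample size. The downside is that differences in effect between hospitals are examined only as exploratory.
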